#### Safety

Safety assessments will include vital sign monitoring, routine blood tests, blood biochemistry, routine urine tests, pregnancy tests, physical examinations, and the recording of adverse events (including serious adverse events). Participants will be monitored for their vital signs, adverse events, and serious adverse events throughout the research period. Routine blood and urine tests and blood biochemistry will be conducted at the time of screening and during the 4th week of treatment. Pregnancy tests will be conducted only at the time of screening. Physical examinations will be conducted at the time of screening, during the 4th week of treatment, and throughout the follow-up period (Table 2).

**Table 2 Tab2:** Timeline for a randomized trial evaluating fire needle therapy for blood stasis syndrome of plaque psoriasis

	Research cycle	Screening period	Baseline period	Treatment period				Early termination	Follow-up period	
	Time point	Week 1	Week 0	Week 1	Week 2	Week 3	Week 4		Week 6	Week 8
**Enrollment**	**Inclusion/exclusion criteria**	**●**	**●**							
	**Informed consent**	**●**								
	**Demographic characteristics**	**●**								
	**Medical history**	**●**								
	**Registration**	**●**								
	**Randomization**		**●**							
	**Photographs of skin lesions**		**●**	**●**	**●**	**●**	**●**	**●**	**●**	**●**
**Interventions**	**Basic therapy + fire needle therapy**		**★-------------------------------------------------------------------★**							
	**Basic therapy + fire needle control therapy**		**☆-------------------------------------------------------------------☆**							
**Assessment**	**PASI**	**●**	**●**	**●**	**●**	**●**	**●**	**●**	**●**	**●**
	**BSA**	**●**	**●**	**●**	**●**	**●**	**●**	**●**	**●**	**●**
	**PGA**	**●**	**●**	**●**	**●**	**●**	**●**	**●**	**●**	**●**
	**DLQI**		**●**	**●**	**●**	**●**	**●**	**●**		
	**PRQoL**		**●**	**●**	**●**	**●**	**●**	**●**		
	**VAS**		**●**	**●**	**●**	**●**	**●**	**●**	**●**	**●**
	**TCM symptom**		**●**	**●**	**●**	**●**	**●**	**●**		
	**Recurrence rate**								**●**	**●**
**Safety**	**Vital signs**	**●**	**●**	**●**	**●**	**●**	**●**	**●**	**●**	**●**
	**Blood routine**	**●**					**●**	**●**		
	**Blood biochemistry**	**●**					**●**	**●**		
	**Urine routine**	**●**					**●**	**●**		
	**Concomitant medication**	**●**	**●**	**●**	**●**	**●**	**●**	**●**		
	**Pregnancy test**	**●**								
	**Physical examination**	**●**					**●**	**●**	**●**	**●**
	**Adverse events**		**●**	**●**	**●**	**●**	**●**	**●**	**●**	**●**
	**Serious adverse events**	**●**	**●**	**●**	**●**	**●**	**●**	**●**	**●**	**●**

*PASI* Psoriasis Area and Severity Index, *BSA* body surface area, *PGA* Physician Global Assessment, *DLQI* Dermatology Life Quality Index, *PRQoL* patient-reported quality of life, *VAS* visual analog scale, *TCM* traditional Chinese medicine

★: Fire needle therapy group

☆: Fire needle control therapy group

### Sample size

In this study, the estimated post-treatment PASI score for all patients will be set at 50% lower than the pre-treatment score, both in the intervention group and the control group. The sample size of the current trial is calculated based on the following formula, and take the cure rate as the primary treatment effect index.
$$ n=\frac{p_1\times \left(1-{p}_1\right)+{p}_0\times \left(1-{p}_0\right)}{{\left({p}_1-{p}_0\right)}^2}{\left({z}_{\alpha /2}+{z}_{\beta}\right)}^2 $$

According to a previous study titled “Therapeutic Observation of Fire-needle Acupuncture for Stationary Plaque Psoriasis” [19], the cure rate to achieve this score is 76.8% for the intervention group and 35.3% for the control group. In this study, we set the inspection level (*α*) as 0.05, and the test power as 0.9, then *β* = 1–0.9 = 0.1. For two-sided tests, at least 25 participants would be required for each group. Considering the correlation of primary outcomes at different times and multicenter effect, we increase the sample size to 38 participants in each group, Considering a dropout rate of 20%, a total of 94 patients (47 per group) will be required for this study (Table 3).

**Table 3 Tab3:** Centers involved in a randomized trial evaluating fire needle therapy for blood stasis syndrome of plaque psoriasis

Research center	Sample size
Shaanxi Hospital of Traditional Chinese Medicine	20
Yueyang Hospital of Integrated Traditional Chinese and Western Medicine	20
First Affiliated Hospital of Heilongjiang University of Traditional Chinese Medicine	18
Affiliated Hospital of Jiangxi University of Traditional Chinese Medicine	18
Traditional Chinese Medicine Hospital of Shijiazhuang	18

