**Methods:**

Ninety-two patients with blood stasis syndrome (BSS) of plaque psoriasis will be enrolled and randomly assigned to receive fire needle therapy (intervention group) or fire needle control therapy (control group) once a week for 4 weeks. The Psoriasis Area and Severity Index (PASI) score will serve as the major efficacy index, while the body surface area (BSA), Physician Global Assessment (PGA) score, Dermatology Life Quality Index (DLQI) score, patient-reported quality of life (PRQoL), visual analog scale (VAS) score for itching, TCM symptom score, and relapse rate will be assessed as secondary outcomes. The PASI score, BSA, PGA score, and VAS score for itching will be evaluated at baseline and during the 4-week treatment and follow-up periods. DLQI score, PRQoL, and TCM symptom score will be assessed at baseline and during the treatment period. Recurrence will be evaluated during the follow-up period. Safety assessments include vital sign monitoring, routine blood tests, blood biochemistry, routine urine tests, pregnancy tests, physical examinations, and adverse-event recording. SAS software will be used for data analysis. The data network platform will be designed by the data management center of Nanjing Ningqi Medical Technology Co., Ltd.

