### Outcomes

#### Primary outcomes

The Psoriasis Area and Severity Index (PASI) is the gold standard assessment tool used to quantify the severity of psoriasis based on erythema, infiltration, scaling, and the extent of lesions [16]. As such, a decrease in the PASI score has been designated as the primary outcome of this study. This score will be evaluated at screening, at baseline, during the 4-week treatment period, and during the 4-week follow-up period. The researchers will use the PASI to assess the severity and area of lesions and simultaneously obtain photographs of typical skin lesions.

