### Statistical analysis

A statistician will formulate a plan for statistical analysis in consultation with the PI. All analyses will be conducted using SAS statistical software, and the data network platform will be designed by the data management center of Nanjing Ningqi Medical Technology Co., Ltd., which will be entrusted with the third-party statistical analyses. The measurers will be blinded to the results. The overall principles will be as follows: An intention-to-treat (ITT) and per-protocol analysis will be used for statistical analysis. Quantitative variables (such as PASI, BSA, PGA, DLQI, PRQoL, VAS, and TCM syndrome scores) will be expressed as mean and standard deviation values or as median values with lower (Q1) and upper (Q3) quartiles. If the quantitative variables conform to normal distribution, a *t* test will be used (The homogeneity test will be performed for the two groups, with 0.05 as the significance level. The Satterthwaite method will be used to correct the *t* test when the variance is not uniform). If quantitative variables conform to skewed distribution, a nonparametric test will be used. Qualitative variables (such as cure rate, recurrence rate) will be expressed as numbers and percentages or composition ratios. Statistical inference will be performed using chi-square tests, Fisher’s exact tests, and Wilcoxon rank sum tests, among others. Potential confounding factors affecting the main outcome indicators will be adjusted by logistic regression. In this study, a *p* value of less than 0.05 is considered as statistically significant.

To account for missing data, we considered participants who may not complete the follow-up when calculating the sample size. The reasons, main characteristics, and data of a patient’s failure to follow-up will be recorded. Other types of randomly missing data will be considered unsuccessful according to the principle of ITT analysis.

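### The 90% power belongs to a binary 50% PASI response, but the declared primary outcome is the decrease in PASI score, so two unranked primaries compete and power for the declared one is unstated

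*Protocol article*

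**What the plan says.** All references are to the protocol article.

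- **Primary outcomes:** "a decrease in the PASI score has been designated as the primary outcome of this study". The abstract agrees: "The Psoriasis Area and Severity Index (PASI) score will serve as the major efficacy index".
- **Sample size:** the instruction is to "take the cure rate as the primary treatment effect index". The threshold is a PASI score halved from its pre-treatment value, and "the cure rate to achieve this score is 76.8% for the intervention group and 35.3% for the control group". For these rates, "we set the inspection level (*α*) as 0.05, and the test power as 0.9". The section derives 25 per group (two-sided), raises this to 38 for correlation between time points and for centre effects, and reaches 47 per group after a 20% dropout allowance.
- **Secondary outcomes:** BSA, PGA, itch VAS, DLQI, PRQoL, TCM symptom score and recurrence. Cure rate is absent.
- **Statistical analysis:** PASI is listed as quantitative, with a t test if normal and a nonparametric test if skewed. Cure rate appears only as an example: "Qualitative variables (such as cure rate, recurrence rate) will be expressed as numbers and percentages or composition ratios". The same section adjusts the main outcomes for confounders by logistic regression and counts some missing data as failures.

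**The concern.** A power statement should describe the analysis on which the trial will be judged. Here the outcome sections name a continuous measure, and the sample size section names a binary one and calls it primary. The analysis section offers methods for both without ranking them: t and rank tests suit a PASI decrease, while logistic regression and counting missing data as failure suit a responder outcome.

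Two things are at stake. First, both measures have a textual claim to be primary and each would be tested at 0.05, so a positive result could be claimed on whichever succeeds. They can disagree, because cutting at 50% discards information and depends on baseline PASI. Second, the quoted 90% gives the reader no information about the outcome that the article declares primary. A lesser point is that calling a 50% reduction a cure would overstate the result if it were reported in that word.

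**Working it through.** **Inputs from the Sample size section:** p1 = 0.768, p0 = 0.353, two-sided α = 0.05, power 0.90; 25 per group, raised to 38. **Not given anywhere:** a mean difference or SD for PASI, a correlation between time points, or a centre effect.

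**1. Reproduce the plan's figure.** With its own formula:

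n = [0.768 × 0.232 + 0.353 × 0.647] / (0.768 − 0.353)² × (1.960 + 1.282)²
= (0.1782 + 0.2284) / 0.1722 × 10.51 = 24.8, so 25 per group.

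The same formula gives 90.2% power at 25. The stated figure is correct for the binary endpoint.

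**2. Which endpoint each section uses.**

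| Section | Endpoint or method | Type |
|---|---|---|
| Abstract, Primary outcomes | PASI score or its decrease | continuous |
| Sample size | 50% PASI reduction | binary |
| Secondary outcomes | no cure rate | – |
| Statistical analysis, tests for PASI | t test or nonparametric | continuous |
| Statistical analysis, adjustment and missing data | logistic regression; missing counted as failure | binary |

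**3. Size of the dual-primary problem.** If success on either test at 0.05 counted, the false-positive rate is bounded by 0.05 + 0.05 = 0.10. The true value is lower because both measures come from the same PASI scores. The documents do not allow an exact figure.

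**4. Power for the PASI decrease.** This needs an assumed standardised difference d. Noncentral t, two-sided 0.05:

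| d (assumed) | 38 per arm, independent | 25 per arm (38 reduced by the 38/25 allowance) |
|---|---|---|
| 0.3 | 25% | 18% |
| 0.4 | 41% | 28% |
| 0.5 | 58% | 41% |
| 0.6 | 73% | 55% |
| 0.7 | 85% | 68% |
| 0.8 | 93% | 79% |
| 1.0 | 99% | 93% |

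The second column assumes that the allowance, 38/25 = 1.52, applies to the t test exactly as to the binary comparison. The d giving 90% power is about 0.75 in the first case and about 0.94 in the second. The normal approximation (1.960 + 1.282) × √(2/n) gives 0.74 and 0.92.

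**5. The only effect size that can be tied to the plan's rates.** If PASI change were normal with equal SD in both arms, and the rates came from cutting it at one threshold, then d = Φ⁻¹(0.768) − Φ⁻¹(0.353) = 0.732 + 0.377 = 1.11. A t test would then have 99.8% power at 38 per arm and 97% at 25. Normality and equal SD are assumptions.

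**The case against.** The strongest reply is that the responder rate really is the main analysis. The sample size section calls it primary, and the logistic regression and the failure rule for missing data fit it. On that reading the power statement is attached to the right endpoint. This has weight. It shows that the conflict may be settled in either direction, and that demoting the responder rate is not the only answer. It does not remove the conflict, because the Primary outcomes section and the abstract say otherwise and the cure rate is in neither outcome list.

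The documents do not support three stronger readings that a reader might infer:

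- **That the binary endpoint has 98% power rather than the stated 90%.** The formula does give 98.0% at 38 independent patients per arm. But 90% is stated for 25 per arm, and the rise to 38 is an allowance for time correlation and centre effects. At face value, 38 then carry the information of 25, and 90% stands.
- **That the plan assumes no treatment effect.** A 50% fall "will be set at 50% lower than the pre-treatment score, both in the intervention group and the control group" sounds like a null assumption. The later phrase about the rate achieving this score, with different rates by arm, shows that it is an awkwardly worded responder threshold.
- **That the trial is underpowered.** The low powers in the table use values of d that have no source in the documents.

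It is also fair to say that the t test is conditional on normality. Neither it nor the nonparametric alternative is the two-proportion comparison used for sizing.

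**Conclusion.** The point stands as a mismatch of endpoints. The stated 90% power is correctly computed for the 50% PASI response and does not describe the declared primary outcome. Power for the PASI decrease is unstated: at 38 per arm it runs from 25% to 99% for assumed d from 0.3 to 1.0 with independent patients, and from 18% to 93% if the allowance is carried over. It would be above 99% (97% with the allowance) if the quoted rates reflect equal-variance normal changes. No shortfall is shown. What must be settled is which result decides the trial, since two unranked primaries leave that open. The 0.75 and 0.94 SD figures are back-calculated from the sample size; they are not target effects found in the protocol.

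**What to change.** Before unblinding, name one primary endpoint at one time point, and align the abstract, Primary outcomes, Sample size and Statistical analysis sections with it. Either choice is sound:

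- **(a) Responder rate primary.** Make the proportion with a 50% PASI reduction primary, with a named two-proportion test, and PASI change secondary. This keeps the existing sample-size basis. The choice of test matters a little: with pooled variance the base is 28 per arm, and with continuity correction 33. Both fit within 38 but leave less for time and centre effects (38/28 = 1.36; 38/33 = 1.15).
- **(b) PASI decrease primary.** Make the responder rate a named secondary outcome. Restate the power for a stated standardised difference, marked as an assumption: 90% at about 0.75 SD if the 38 per arm are treated as independent, or at about 0.94 SD if the 38/25 allowance is assumed to carry over. Say which is meant.

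In both cases, rewrite the opening sentence of Sample size as the responder definition, and call the endpoint a 50% PASI response instead of cure.

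The cost is a protocol amendment, which the Quality assurance system section sends to the IRB of each centre, in a trial that began recruiting in June 2019. No extra patients are needed. Under (a) the declared primary outcome changes during the trial and this must be reported openly; under (b) the power claim becomes conditional on an assumed effect.

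### The abstract enrols 92 patients, but the sample-size section and the Table 3 centre quotas require 94

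*Protocol article*

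**What the plan says.** The Methods paragraph of the abstract states: "Ninety-two patients with blood stasis syndrome (BSS) of plaque psoriasis will be enrolled and randomly assigned".

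The Sample size section builds its total in three steps.

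- From the assumed response rates ("the cure rate to achieve this score is 76.8% for the intervention group and 35.3% for the control group"), with two-sided α = 0.05 and power 0.9, it finds that "at least 25 participants would be required for each group".
- For correlation of the primary outcome over time and for the multicentre effect, "we increase the sample size to 38 participants in each group".
- For dropout: "Considering a dropout rate of 20%, a total of 94 patients (47 per group) will be required for this study".

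Table 3, in the same section, allots 20, 20, 18, 18 and 18 patients to the five centres.

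**The concern.** Both figures describe the same quantity. The abstract speaks of patients enrolled and randomised; the Sample size section gives its total after adding the dropout allowance. Neither is a number of completers, so the difference cannot be explained as before versus after dropout. Nor is it a matter of an article condensing a longer protocol, because both numbers stand in the article and they disagree.

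The total defines when recruitment is complete, and it is the number against which the final report will be checked. With two published totals there is no single planned figure for that check. The abstract's lower figure also falls short of the plan's own target of 38 per arm once 20% are lost.

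**Working it through.** **Inputs** (Sample size section unless noted): p₁ = 0.768, p₀ = 0.353, two-sided α = 0.05, power 0.90; 25 per group, raised to 38; dropout 20%; total 94 (47 per group); Table 3 quotas; total 92 (abstract).

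**1. The plan's base figure.** The stated formula is n = [p₁(1−p₁) + p₀(1−p₀)] / (p₁−p₀)² × (z_{α/2} + z_β)².

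- Numerator: 0.768 × 0.232 + 0.353 × 0.647 = 0.4066
- Squared difference: 0.415² = 0.1722
- (1.960 + 1.282)² = 10.507
- n = 0.4066 / 0.1722 × 10.507 = 24.80, rounded up to 25

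This reproduces the stated 25 per group.

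**2. Centre quotas.** 20 + 20 + 18 + 18 + 18 = 94. Table 3 agrees with the text of its section.

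**3. Dropout allowance from 38 per group.**

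- Dividing by the retained fraction: 38 / (1 − 0.20) = 47.5 per arm. The stated 47 lies half a patient below this; strict rounding up gives 48 (96 in total).
- Multiplying instead: 38 × 1.2 = 45.6, rounded up to 46 per arm, or 92 in total. This equals the abstract's figure, but the article does not say that 92 was obtained in this way.

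**4. What each total leaves at 20% dropout.** Power uses the plan's formula at its assumed rates. The first power column applies no design effect. The second assumes that the whole increase from 25 to 38 is used up by correlation and centre effects, so the retained number is multiplied by 25/38.

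| Total | Per arm | Left per arm | Largest dropout that keeps 38 | Power, no design effect | Power, n × 25/38 |
|---|---|---|---|---|---|
| 92 | 46 | 46 × 0.8 = 36.8 | 1 − 38/46 = 17.4% | 97.7% | 89.3% (n = 24.2) |
| 94 | 47 | 47 × 0.8 = 37.6 | 1 − 38/47 = 19.1% | 97.9% | 89.9% (n = 24.7) |
| Target | – | 38 | – | 98.0% | 90.2% (n = 25) |

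Under either assumption, 92 costs less than one percentage point of power against the target of 38, and 94 costs less than half a point.

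**The case against.** The strongest reply is that the difference is two patients, that the operative section and the centre quotas agree, and that only a summary is out of line. All of that stands. It limits the consequence and shows which figure to keep, but it does not remove the contradiction.

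A second reply is that 38 completers per arm is not a stated requirement. The Statistical analysis section plans an intention-to-treat analysis and counts certain missing data as unsuccessful, so the denominator of a responder analysis could stay near the number randomised. As a check, suppose that 20% drop out in each arm and all count as failures. The rates become 0.8 × 76.8% = 61.4% and 0.8 × 35.3% = 28.2%, and the plan's formula without a design effect gives about 93% power at 47 per arm and 92% at 46. On that basis neither total falls below the planned 90%. This too bears on the size of the problem, not on whether the two totals agree.

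Three stronger readings are tempting, and the document does not support them.

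- *A reader might infer that 96 patients are needed and that 94 fails as well.* The gap is 47 against 47.5 per arm, or 37.6 against 38 expected completers, under a round planning value for dropout. Moreover, 47 need not be a slip. An allowance of 1.5 carried unrounded reproduces every stated figure with ordinary rounding up: 24.80 × 1.5 = 37.2, giving 38, and 37.2/0.8 = 46.5, giving 47. Starting from 25 gives 37.5 and 46.9, hence the same 38 and 47. The factor 1.5 is an assumption, since the section names none, but it means that 47 cannot be called wrong with confidence.
- *A reader might infer that 92 comes from multiplying 38 by 1.2.* The match is exact, but a figure left over from an earlier protocol version would explain it equally well; the Trial status section describes the text as version 3.0.
- *A reader might infer room to choose the stopping point late in recruitment.* The Quality assurance system section does plan an interim analysis in the second year, with results shared among the centres. Nothing in the article ties the end of enrolment to such a choice, however, and two patients give no meaningful scope for it.

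**Conclusion.** The point holds as an internal inconsistency. The article states an enrolment total of 92 in the abstract and 94 in the Sample size section, and Table 3 supports 94. At 20% dropout the lower figure leaves 36.8 per arm, 1.2 below the stated 38. The loss of power is about 0.3 percentage points without a design effect (98.0% to 97.7%), or about 0.9 points if the step from 25 to 38 is wholly used up by correlation and centre effects (90.2% to 89.3%). These figures rest on the plan's assumed response rates, equal allocation and dropout that is equal in the two arms.

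The matter is worth correcting because the total is a basic planned figure, not because the trial would be underpowered. The rounding of 47.5 to 47 is a minor remark: 0.4 of an expected completer per arm, with negligible effect on power.

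**What to change.** Correct the abstract from 92 to 94, so that the abstract, the Sample size section and Table 3 state one enrolment total. If the sponsor in fact holds 92 to be the target, the Sample size section and Table 3 would have to change instead, with the reason given.

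Optionally, word the allowance to match the arithmetic, for example: 47 per group keeps 38 if dropout is at most about 19%. If an unrounded inflation factor was used to reach 38 and 47, naming it would serve equally well.

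The cost is a change of wording. No patients are added, and no centre quota or analysis changes.
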